**Demographic Variables**
• Age < 39 years versus > 39 years,
• Intellectual versus physical demanding job,

**Anamnestic and Neurological Variables**
• Acute start LSRS versus slow start,
• History of backpain versus no history,
• Influence of coughing, sneezing on complaints versus no influence,
• Difficulty to put on shoes and/or socks versus no difficulty,
• Straight leg raising ≤ 30 degrees versus > 30 degrees,
• Positive crossed straight leg raising sign versus negative sign,
• VAS-pain > 70 versus < 69 mm,
• Tingling/numbness in pain area versus no tingling (9),
• Pain leg worse by sitting versus no worsening (9),
• McGill affective high score versus low score,

**Radiological Variables**
• MRI disc sequester versus contained disc herniation,
• MRI circumferential gadolinium enhancement versus no enhancement of disc herniation,
• Mediolateral versus median and lateral disc herniation,
• High versus low height of disc level (height 9 mm),

**Miscellaneous Variables**
• Preference for surgery versus no preference for surgery.
• Disc Herniation at L5S1 vs. L4L5

Using logistic regression for success rate and linear regression for severity of the disability, each prognostic indicator is checked for interaction with treatment. If the interaction term is significant, a stratified analysis will be performed.

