The lumbosacral radicular syndrome (LSRS or LRS; also called sciatica) is typically characterized by radiating pain in the dermatome of a lumbar or sacral spinal nerve root. Occasionally more than one root is involved. Contained in the syndrome pain may be accompanied with lumbar fixation, reflex abnormalities motor and sensory disturbances. In diagnosis includes stenosis of the spinal and/or root canal, infection, multiple sclerosis, autoimmune or metabolic neuropathy, and tumour. This study will be restricted to herniations at the lowest three lumbar disc levels, since these represent the most common sites. In the vast majority of cases LSRS is the result of a herniated disc. In the Netherlands annually between 60,000 and 75,000 new cases of LSRS are diagnosed by the General Practitioner (GP) [3]. The presumed direct medical costs of treatment of LSRS are € 133 million each year [4]. Most of these costs are attributable to in-hospital treatment; only a small portion is incurred by GP's or physiotherapists (€ 3.2 million). In a study, performed in 1988, more than 11.000 patients were operated in the Netherlands and this frequency did not change in the past years [4,5]. The combined direct and indirect costs are estimated to be € 1,2 billion per year [6]. The indirect costs are considerable due to the high rate of production loss caused by sciatica.

The natural history of LSRS is in general favourable. In 60–80 percent of patients, the leg pain decreased or disappeared within 6–12 weeks after onset [7-9,51]. These patients no longer experienced problems at work or in their private lives after three months. The minority with lasting complaints beyond three months further decreases with time. At one year only a small proportion of herniated discs continues to produce discomfort and disability. At present it is not possible to identify these latter groups of patients in an early stage of their disease by means of intensity of pain, neurological deficit, root irritation signs, or diagnostic imaging. For this reason it is not helpful to perform early diagnostic imaging (CT or MRI), unless a disease entity different from disc herniation is considered. After the indication for surgery has been set diagnostic imaging is helpful in defining the exact site of disc herniation and its anatomical relationship with the nerve root involved.

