The result of this study will be a trade off between the disadvantages of surgery (hospitalisation, reduced quality of life and costs) versus the possible advantages (earlier relief of pain and return to work). For that reason recovery, measured as an 11 point difference in score when compared to baseline (Roland Disability Questionnaire for Sciatica), is the clinically most relevant patient outcome. Quality of Life (SF-36) and perceived recovery are important to compare the reduced quality of life from surgery to the possibly prolonged pain from conservative therapy and also to be able to compare cost-effectiveness with that of other spine interventions. The EuroQol is important to obtain cost-utility ratio's that can be compared with those of a wide range of other interventions. Utilities are obtained from the descriptive classification system of the EuroQol, using the model described by Dolan [43,53]. Conservative treatment may decrease costs compared to surgery but possibly at the expense of delayed effectiveness. In an incremental cost-effectiveness analysis, societal costs during the first year will be compared to the primary outcome measure (Roland Disability Questionnaire for Sciatica, averaged over the first year), Quality of Life (SF-36, during the first year) and perceived recovery (7-points Likert scale). Cost-effectiveness analyses with these effectiveness measures have been conducted before, allowing comparison with other spine interventions.

Finally, to answer the second research question explorative analyses are conducted to investigate whether the treatment effect after two, six and twelve months varies in specific subgroups of patients (Table 3).

**Table 3 T3:** Selected prognostic variables for subgroup analysis

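### The exploratory subgroup plan lets significance in 108 interaction tests pick which subgroups are shown, and some of its categories leave patients in no group

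*Protocol article*

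**What the plan says.** The Background gives the identification of possible subgroups that benefit substantially from one strategy as a secondary goal. Statistical and cost analysis states the plan for it: "explorative analyses are conducted to investigate whether the treatment effect after two, six and twelve months varies in specific subgroups of patients". Table 3 lists the modifiers, each as a two-group contrast: 2 demographic, 10 from history and neurological examination, 4 radiological and 2 miscellaneous.

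The text after the table names the two models: "Using logistic regression for success rate and linear regression for severity of the disability, each prognostic indicator is checked for interaction with treatment". It then gives the decision rule: "If the interaction term is significant, a stratified analysis will be performed". It states neither a significance level nor an adjustment for the number of tests.

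Three of the contrasts read:

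- "Age < 39 years versus > 39 years"
- "VAS-pain > 70 versus < 69 mm"
- "Disc Herniation at L5S1 vs. L4L5"

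On eligible levels the Background says: "This study will be restricted to herniations at the lowest three lumbar disc levels".

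**The concern.** Three features of the plan work against its aim.

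1. Many interaction tests are run, and the significant ones decide which subgroups receive a stratified analysis. Such a screen tends to display chance findings, and it leaves the remaining estimates without a stated place in the report.
2. The trial was sized for its main comparison. A real interaction as large as the main target difference would more often be missed than found.
3. Some categories do not cover all eligible patients, and five measured quantities (age, leg-pain VAS, straight-leg-raising angle, McGill affective score, disc height) are reduced to two groups.

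The article expects the trial to inform referral decisions by general practitioners and neurologists, so a subgroup result from this screen could be read as guidance on whom to refer for surgery. Its opening paragraphs also note that non-significant results are less often published. A significance trigger repeats that selection inside the trial.

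**Working it through.** **The plan's own figure.** The article states no test count or error rate for the subgroup analyses. The nearest figure is in Sample size: difference 4, SD 10, two-sided α 0.05, power 0.90, 140 per arm. Those inputs give 132 per arm, and 140 per arm gives power 0.917. The stated number is therefore slightly conservative, and this has no bearing on the present point.

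**Number of tests.** Modifiers: 2 + 10 + 4 + 2 = 18. Models: 2. Time points: 3. Total: 18 × 2 × 3 = 108.

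**False positives.** Assume α = 0.05 per test (the article gives this level only for the sample size) and no true interaction.

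- Expected number: 108 × 0.05 = 5.4, whatever the correlation between tests.
- Chance of at least one if all tests were independent: 1 − 0.95^108 = 0.996.
- Chance of at least one with a single test per modifier, independent: 1 − 0.95^18 = 0.60.

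The six tests on one modifier share patients and related outcomes, so 0.996 is an upper figure. Simulating 18 modifiers with six correlated z-tests each, under assumed correlations, gives this chance of at least one false positive:

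| Correlation within a modifier | Modifiers independent | Modifiers correlated 0.3 |
|---|---|---|
| 0.5 | 0.98 | 0.97 |
| 0.8 | 0.93 | 0.88 |
| 0.9 | 0.87 | 0.80 |
| 0.95 | 0.81 | 0.72 |
| 1 | 0.60 | 0.51 |

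**Power for a real interaction.** Patients analysed: 300 × 0.92 = 276. For a modifier split 50:50, SE = 4 × 10/√276 = 2.41. Power for a 4-point interaction is Φ(4/2.41 − 1.96) = 0.38. With 280 patients it is 0.39. With 280 patients and a 25:75 split it is 0.30.

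**Effect of a strict correction.** At 0.05/18 = 0.0028, with 280 patients and a 50:50 split, power for 4 points falls to 0.09. For 8 points it falls from 0.92 to 0.64.

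**Gaps in the categories.** Eligible ages run from 18 to 65, which is 48 whole years. If ages were uniform, age 39 would hold 1/48 = 2.1%, about 6 of 280 patients. On a 100 mm scale read in whole millimetres there are 101 values. If these were uniform, 69 and 70 mm would hold 2/101 = 2.0%, again about 6 of 280. Uniformity is only an illustration. The disc-level contrast names two of three eligible levels, and the share at the third is not given. The straight-leg-raising contrast (at or below 30 degrees against above) has no gap, so the gaps elsewhere are drafting faults.

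**Cost of dichotomising.** For a normally distributed modifier that acts linearly, a median split keeps 2/π = 0.64 of the information. The article does not say that its cuts are medians, so 0.64 is a guide for the five measured variables and not an estimate for each.

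**The case against.** The strongest reply is that the article calls these analyses exploratory and speaks only of possible subgroups. No confirmatory error rate is claimed, so none is breached. The modifiers are listed in advance, and an interaction test comes before any stratified analysis, which is better than comparing p-values within subgroups. The level, and any correction, could stand in an analysis plan that is not shown. All of this stands, and the absence of a correction is not treated as an error here.

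Three stronger readings are tempting, and the document supports none of them.

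- A reader might infer that false subgroup findings are near certain. That needs nearly independent tests at 0.05. Correlation lowers the figure, and the level itself is an assumption.
- A reader might infer that dichotomising creates spurious subgroups. A cut-point fixed in advance costs power but does not raise the false-positive rate of an interaction test in a randomised trial.
- A reader might infer that the gaps remove many patients. For age and VAS the loss is small under the uniform illustration. The article does not say how such patients are handled, and the notation may simply be loose. The disc-level line may be meant as a contrast of two named levels.

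The exploratory label does not answer everything. It does not place a patient aged 39 in a group or recover the information lost by the cuts. Nor does it justify letting significance choose which subgroup results are worked out, since exploratory results are most useful when all of them are visible.

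**Conclusion.** The point holds as a weakness in how an exploratory analysis is specified. It does not threaten the main comparison.

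The count of 108 tests, the significance trigger and the incomplete categories follow from the text. The expectation of 5.4 false positives rests on a level of 0.05 and no true interaction. The chance of at least one, about 0.5 to 0.99, also rests on the assumed correlations. Likely is a fair word for it over most of that range. Power of about 38% rests on the article's SD of 10, a 4-point interaction, 276 patients and an even split.

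Under those assumptions the screen would be expected to yield several chance results while missing most real interactions of the size that the trial treats as important. A stratified result selected in this way would be weak ground for advice on referral.

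**What to change.** Amend Table 3 and the sentences that follow it.

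1. Make the categories exhaustive: assign age 39 and VAS 69 to 70 mm to a group, and give the third disc level a place.
2. Enter age, leg-pain VAS, straight-leg-raising angle, McGill affective score and disc height as continuous modifiers, and keep cut-points for display only.
3. Report all 18 interaction estimates with confidence intervals, labelled exploratory and with the number of tests stated. Remove the rule that significance decides which subgroups are shown.

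A formal multiplicity correction is optional, because it would cut power for a 4-point interaction to about 9% at 0.05/18. Restricting the tests to twelve months is also optional. It reduces their number but gives up the earlier effects in a trial about timing.

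No new patients, visits or data are needed. The costs are slightly more reporting, an assumed functional form for the continuous modifiers, and fewer subgroup results that can be presented as significant.

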## Discussion

In this article the rationale and design of a pragmatic RCT on the cost-effectiveness of timing of disc surgery for LSRS is described. The only randomized trial [7] so far on this subject only included patients where the caregiver was in doubt about the surgical indication. Patients with severe disabling pain were not randomized [8]. The Sciatica Trial is directed to those patients with a clear surgical indication according to current usual care. The study is pragmatic because it acknowledges that sometimes it may not be possible to postpone surgery for every conservative care patient until 6 months after allocation and that some patients will recover before surgery is performed in the surgical group. In these cases we consider it unethical to hold on to the randomized treatment. Because of the Intent-to-Treat analysis these cases will be analysed in their own allocated randomization arm and will not cause methodological problems because it is two healthcare strategies that are compared, as opposed to two treatments. The objective of this trial is to provide evidence on the preferred timing of disc surgery for sciatica. A prolonged conservative treatment strategy is compared to the international guideline advise of surgery after 6–8 weeks LSRS. The intended size of the study population is sufficiently large to detect short and long term differences between both strategies.

## Abbreviations

GP = General Practitioner

LSRS = Lumbosacral Radicular Syndrome

RCT = Randomized Controlled Trial

VAS = Visual Analogue Scale
